**Figure 3 figure3:**
[figure not shown]
Study design and planned participant flowchart. BG: Berufsgenossenschaft; ECG: electrocardiogram; PAR-Q+: The Physical Activity Readiness Questionnaire for Everyone; SCIM III: Spinal Cord Independence Measure III; SF-36: Short Form–36 Health Survey.

### Participants

#### Eligibility Criteria

Participants are eligible for the study if they meet the following inclusion criteria: (1) chronic paraplegia (time since injury >1 year), (2) age between 18 and 67 years, (3) sufficient German language skills, (4) ability to provide informed consent, and (5) access to a smartphone. Participants will be excluded from the trial if they have any of the following conditions or diseases: (1) acute infection or inflammation (eg, urinary tract infection or pressure ulcers), (2) uncontrolled hypertension or diabetes, (3) manifest cardiovascular diseases, (4) psychiatric or mental conditions that compromise informed consent or may interfere with the study results (eg, major depression and psychotic disorders), (5) ongoing alcohol or substance abuse, and (6) other medical contraindications. In addition, they will be excluded if they are high-performance athletes (in the national team).

Potential participants will be enrolled based on the results of the medical screening using their medical records, a resting electrocardiogram, and the Physical Activity Readiness Questionnaire for Everyone (PAR-Q+) [35]. Because participants recruited by the BG clinic Tübingen will not perform exercise tests, a resting electrocardiogram is not required.

#### Randomization

Only the 30 participants recruited at the GSU will be block randomized, stratified by the level (high vs low paraplegia) and completeness (complete vs incomplete paraplegia) of the SCI with a block size of 4. This will be done using Excel (Microsoft Corp). The randomization code will be released after the participant has completed all baseline measures. The randomization list will be password protected. Only JB and AL, who conduct the randomization and allocation, will have access to the list. No randomization is required at the BG clinic Tübingen, as data collection at that site focuses on the primary outcomes.

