**Methods:**

This pilot block-randomized controlled feasibility trial will include 45 adult participants with paraplegia. Eligible participants will be block randomized to either the intervention or waitlist control group. The intervention group will perform a 6-week exercise program using the ParaGym mobile exercise app, comprising three 35-minute exercise sessions per week. The waitlist control group will continue their usual care and receive access to the app after study completion. Participants will record all exercise sessions conducted with the app as well as additional exercise sessions conducted during the study period using exercise diaries. The primary outcomes include feasibility, usability, and safety. Feasibility will be assessed through semistructured interviews, study adherence, and retention rates. Usability will be measured using the System Usability Scale. Safety will be determined by the occurrence of adverse events. Secondary outcomes include the effects of the intervention on peak exercise capacity (VO_2_ peak); handgrip strength; independence, which will be measured using the Spinal Cord Independence Measure III (SCIM III); and health-related quality of life, which will be measured using the Short Form–36 Health Survey (SF-36).

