### Study Design

This pilot mixed methods block-randomized controlled feasibility trial with an allocation ratio of 1:1 for the intervention and waitlist control groups is conducted at the German Sport University Cologne (GSU), Germany. The trial was registered with the German Clinical Trials Register (DRKS00030370).

Participants will be recruited at the GSU and the SCI center at the BG (*Berufsgenossenschaft*; English: occupational insurance association) clinic Tübingen, Germany. Participants will be recruited at the GSU via the project newsletter, the project website, social media, and by contacting rehabilitation centers and spinal cord associations. The BG clinic in Tübingen will recruit among their patients.

Measurements will be conducted at baseline (t_0_) and after the intervention (t_1_; Table 1). The primary outcomes (feasibility, usability, and safety) will be assessed during the intervention and at t_1_. The secondary outcomes (peak exercise capacity, handgrip strength, independence, and quality of life) will be assessed at t_0_ and t_1_. As data collection at the BG clinic Tübingen will focus on the primary outcomes and owing to limited capacity, the ramp exercise test for evaluating peak exercise capacity and handgrip strength test will be conducted only at the GSU and not at the BG clinic Tübingen. After randomization and group allocation, participants in the intervention group will be provided with the ParaGym mobile exercise app and uptake a 6-week home-based training intervention. The participants will be instructed to complete 3 training sessions per week. For this cohort, resistance training for at least 2 days a week is recommended [2,6]. As the training sessions delivered by the app comprise not only strength but also aerobic and flexibility exercises, we decided to provide training sessions for 3 days instead of 2. Eitivipart et al [34] recommend 3 sessions for a minimum duration of 20 minutes per week over at least 6 weeks to achieve substantial outcomes. The waitlist control group will proceed with their usual care and receive access to the mobile app once they have completed the trial. After the 6-week intervention, participants in the intervention group will be interviewed over the phone to assess feasibility and usability. Subsequently, both groups will return to the study site (t_1_) for the SUS questionnaire and secondary outcome measures. The study design and planned participant flow are presented in Figure 3.

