#### Sample Size

The aim is to recruit a total of 45 participants between November 2022 and January 2023: 30 participants at the GSU and 15 participants at the BG clinic Tübingen. As this is a pilot trial, the sample size was based on previous studies with similar aims and methods [27,28] and recommendations for usability testing [65].

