#### Quantitative Analysis

Quantitative data analysis will be performed using SPSS. All data will be tested for normal distribution using the Shapiro-Wilk test. Study participant characteristics will be presented descriptively by calculating means and SDs for normally distributed variables. Median values and IQR will be calculated for skewed continuous variables, and absolute and relative frequencies will be calculated for nominal variables. Group differences at baseline will be calculated for independent samples using a 2-tailed *t* test, Mann-Whitney *U* test, or chi-square test depending on the distribution and level of measurement. At t_1_, normally distributed continuous variables will be analyzed using a mixed analysis of variance model to test for significant effects for group and time. For skewed continuous variables, Wilcoxon and Mann-Whitney *U* tests will be conducted to test the differences between the groups and between t_0_ and t_1_. The significance level will be set at *P*<.05. Absolute and relative frequencies will be reported for adherence and retention.

Feasibility will be assumed if (1) at least 66% of the training sessions (equivalent to 2 out of 3 sessions per week) are completed [43] and (2) the retention rate is at least 75% [67]. Exercise diaries will be analyzed in terms of the frequency, duration, and intensity of the training sessions. Safety will be assessed by comparing the number of study-related AEs or SAEs in the intervention group with that in the waitlist control group [68].

Spearman correlations will be used to assess the association between performance and strength outcomes and SCIM III and SF-36 outcomes. Subgroup analyses might be conducted for lesion level (high vs low paraplegia) and age. Missing data will not be imputed.

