### Strengths and Limitations

Using the SPIRIT 13 Guidelines [31,72] for reporting the planned trial and the SCI trial guidelines [51,73] for designing as well as randomizing and controlling the trial improves its strength. In addition, the GSU cooperates with the BG clinic Tübingen to reach a larger sample size. Another strength is the compatibility of the app with various operating systems such as iOS (Apple Inc) and Android. However, smartphones should not be older than approximately 5 years to guarantee absolute functionality.

The ParaGym mobile app is currently at a prototype stage. Therefore, only basic functions and features are currently included. This could impact the variety of exercises, especially for users with severe impairments, which may decrease their motivation to use the app. The conclusiveness and generalizability of the results will be limited owing to the small sample size. In addition, only healthy adults with paraplegia were included in the study. Therefore, many individuals will be excluded from the study. Generalizability is also limited because the prevalence of cardiovascular diseases is high in individuals with SCI [74,75]. In addition, not restricting additional sports activities may have a major impact on the postintervention measurement results. Moreover, selecting exercises that are mainly suitable for beginners may compromise the effectiveness for intermediate users. Finally, all exercises will be performed using body weight or a resistance band, which will limit the user’s opportunity to increase intensity compared with using additional weights.

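### The trial is presented as 45 participants block-randomised 1:1, but only 30 are randomised, and the group comparisons, including the one for safety, are not limited to those 30

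*Protocol article*

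**What the plan says.** The abstract gives a sample of 45 and states: "Eligible participants will be block randomized to either the intervention or waitlist control group". Study Design calls the whole trial block-randomised "with an allocation ratio of 1:1 for the intervention and waitlist control groups". Sample Size splits the 45 into "30 participants at the GSU and 15 participants at the BG clinic Tübingen".

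The Randomization section narrows this: "Only the 30 participants recruited at the GSU will be block randomized". Its reason for leaving out the second site is: "No randomization is required at the BG clinic Tübingen, as data collection at that site focuses on the primary outcomes".

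On what is measured where, Study Design says that "the ramp exercise test for evaluating peak exercise capacity and handgrip strength test will be conducted only at the GSU". No other assessment is withdrawn at Tübingen. The same section has Tübingen recruiting from its own patients, while GSU recruits through a newsletter, a website, social media and outside centres. Eligibility Criteria waives the resting electrocardiogram at Tübingen.

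Quantitative Analysis tests baseline differences between groups, then group and time effects on continuous outcomes. It assesses safety by "comparing the number of study-related AEs or SAEs in the intervention group with that in the waitlist control group". It names no site term and does not say whether non-randomised participants enter these comparisons. Strengths and Limitations gives the purpose of the second site: "the GSU cooperates with the BG clinic Tübingen to reach a larger sample size".

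**The concern.** The design statement is wrong for one third of the sample (15/45). That can be read directly from the page and does not depend on any detail left to an analysis plan.

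The reason given for not randomising at Tübingen also fails on the protocol's own terms. A focus on primary outcomes removes the need for a control only if no primary outcome is judged between groups. Safety is a primary outcome, and the stated method for it is a comparison of the intervention group with the waitlist group. Tübingen has no waitlist group.

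An analyst who follows the text could therefore place 15 clinic patients in the app group opposite controls drawn only from GSU. Site and treatment would then be mixed in the safety comparison, in the baseline tests, and in the SCIM III and SF-36 tests if those questionnaires are given at Tübingen. A site covariate would not help, because a site without controls adds nothing to a within-site contrast.

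**Working it through.** **Inputs from the protocol.** 30 GSU participants, randomised 1:1 in blocks of 4 within four strata (lesion level by completeness); 15 Tübingen participants, not randomised; significance level 0.05. The total reproduces: 30 + 15 = 45. There is no power calculation to reproduce.

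**Assumptions.** All 15 Tübingen participants use the app, and they are pooled with the GSU app arm. D is the difference between sites in mean change, in SD units, that has nothing to do with the app. The protocol gives no value for D, so a range is shown.

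**Composition if pooled.**
- App group: 30/2 + 15 = 30. Controls: 15. The ratio is 2:1, not 1:1.
- Non-randomised share of the app group: 15/30 = 50%.
- Incomplete blocks in four strata allow 12 to 18 GSU app users, so the share runs from 15/33 = 45% to 15/27 = 56%.

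**Bias for a continuous outcome.** Bias = (Tübingen share of the app group) × D = 0.5 D at 15:15 within GSU.

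**Type I error.** Simulated two-sample t test on change scores, which is equivalent to the group-by-time test in a two-group, two-time mixed ANOVA. Settings: 30 v 15, no app effect, 15 of the 30 app users shifted by D.
- D = 0.3: bias 0.15 SD, type I error about 7%
- D = 0.5: bias 0.25 SD, about 11%
- D = 0.8: bias 0.40 SD, about 20%
- D = 1.0: bias 0.50 SD, about 28%
- GSU only, 15 v 15: no site bias, 5.0%

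**Adverse event counts.** The plan compares numbers of events. At an equal rate r per person, the expected counts are 30r v 15r, a ratio of 2. At the limits allowed by the blocks, they are 27r v 18r (ratio 1.5) and 33r v 12r (ratio 2.75). With an assumed r = 0.2 and 30 v 15, that is 6 v 3. If the Tübingen rate were 0.4 and the GSU rate 0.2, it would be 15 × 0.2 + 15 × 0.4 = 9 v 3, still with no app effect.

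**Precision lost by restricting to GSU.**
- Pooled: √(1/30 + 1/15) = 0.316 SD
- Randomised only: √(1/15 + 1/15) = 0.365 SD
- Ratio: 0.365/0.316 = 1.155, about 15% larger
- Difference detectable with 80% power (two-sided 0.05, normal approximation): 1.02 SD instead of 0.89 SD

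**The case against.** The best defence is that the protocol never says that Tübingen will be pooled. Study Design has the intervention group receive the app after randomisation and allocation, and only GSU participants are randomised. On that reading the two groups in Quantitative Analysis are the randomised arms, and 1:1 is correct for them. The larger sample is then used for usability, adherence, retention and interviews, where pooling app users is legitimate. The Safety section also rests on intervention-related events, which can be judged among app users alone. The Randomization section discloses the non-randomised site openly.

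Much of this stands, and it limits the point. It does not remove it: the abstract still says something different, and the rule for safety still needs a control group that one site lacks.

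Some stronger readings are tempting but not supported:
- **That SCIM III and SF-36 are certainly collected at Tübingen.** This is inferred from the withdrawal of only two tests there. The safety part does not need it.
- **That Table 3 (8 intervention, 4 control) shows pooling has begun.** If all 12 were GSU participants, stratified blocks of 4 would give a gap of 4 or more towards the app with probability 0.076, one-sided. Chance is a fair explanation, and a descriptive table does not show how outcomes will be tested.
- **That the type I error figures apply to safety.** No test is named for adverse event counts.
- **That the participant flow chart is wrong.** Figure 3 was not available for this review and may already separate the sites.

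**Conclusion.** The point holds as a contradiction in the design statement, joined to a set of group comparisons whose population is left open. The contradiction is certain. The confounding is conditional on pooling, on app use by all 15 Tübingen participants and, for SCIM III and SF-36, on their collection at that site. Under those conditions about half of any site difference becomes an apparent app effect. Its size depends on D, for which the documents offer nothing; the figure of 28% needs a full SD and is an upper illustration.

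This should be fixed, but a reader who inferred that it undermines the trial would go too far. This is a pilot. Its usability, adherence and retention criteria are thresholds rather than contrasts between groups. The effects on independence and quality of life are described as preliminary. VO2 peak and handgrip strength are measured only at GSU and are not affected.

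**What to change.** 1. In the abstract and Study Design, state that 45 participants are enrolled, of whom 30 (GSU) are randomised 1:1 and 15 (Tübingen) form a non-randomised single-arm app cohort.
2. In Quantitative Analysis, restrict every between-group comparison to the 30 randomised participants: baseline tests, SCIM III, SF-36, adverse and serious adverse events, and retention by arm.
3. Pool Tübingen with the GSU app users only for single-arm outcomes, shown by site: SUS, adherence, retention among app users, interviews and intervention-related adverse events.
4. Show Tübingen participants in a separate column of the baseline tables.

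The cost is wording and the definition of an analysis set; no new data are needed. If the questionnaires are collected at Tübingen, the SCIM III and SF-36 contrast becomes 15 v 15 instead of 30 v 15, with the standard error about 15% larger as worked above.

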### Data Management and Analyses

#### Data Management

Data will be entered into Microsoft Excel (version 2018) by one researcher and double-checked by another researcher before being analyzed using SPSS Statistics (version 29, IBM Corp). To ensure confidentiality, data will be recorded using the participants’ study ID instead of their names. All data forms will be stored electronically and protected by a password in addition to being stored in paper form and secured in a locker in a room with restricted access. Only the authors of this manuscript will have access to the full data set. The principal investigator (JB) will monitor AEs. The data will be deleted upon participants’ request.

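### The same two people generate the randomisation list, hold it in full and allocate from it; one of them is the principal investigator, who also monitors adverse events.

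*Protocol article*

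**What the plan says.** All of this stands in the protocol article.

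- **Who is randomised.** Under Randomization: "Only the 30 participants recruited at the GSU will be block randomized". Study Design describes the trial "with an allocation ratio of 1:1 for the intervention and waitlist control groups".
- **How.** The sequence is made in Excel, "stratified by the level (high vs low paraplegia) and completeness (complete vs incomplete paraplegia) of the SCI", which gives four strata, "with a block size of 4".
- **Who holds the list.** It is password protected, and only two team members "who conduct the randomization and allocation, will have access to the list".
- **When the code is released.** After the participant has finished all baseline measures.
- **Who monitors safety.** Under Data Management, the principal investigator "will monitor AEs". The initials given there match one of the two list holders.
- **Entry.** Under Eligibility Criteria, enrolment follows a medical screening with records, a resting electrocardiogram and a readiness questionnaire. The exclusions are mostly named conditions, but one is open-ended: "other medical contraindications".
- **Comparator.** Study Design and Intervention describe usual care with access to the app after the final measurements, so the assignment is plain to participants and site staff.

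The article describes no independent list holder, envelopes or central release, and does not say who screens and enrols at the GSU.

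**The concern.** Allocation concealment means that whoever can influence whether or when a person enters the trial cannot know the next assignment. Here generation, custody and allocation lie with the same two people, and the safeguards described are aimed at everyone else. A password keeps others out of the file. Release after baseline protects the baseline measurement from staff who lack the list, but eligibility is settled before baseline, and someone who can open the file has no need to wait for the release.

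A second, smaller route is open to staff without the list. In a waitlist design past assignments are visible, and a single small block size lets anyone who keeps a tally within a stratum work out part of what comes next.

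At stake is the randomised contrast between two arms of about 15. It carries the secondary outcomes (peak exercise capacity, handgrip strength, independence, quality of life). It also carries one primary outcome, because Quantitative Analysis judges safety by comparing the number of study-related events between the arms.

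**Working it through.** The article gives no predictability figure to reproduce, so the check starts from its design inputs: 30 randomised, 1:1, block size 4, 2 × 2 = 4 strata. The stratum sizes are not given and are an assumption, varied below. The guesser is assumed to know the block size, the participant's stratum and the earlier assignments in that stratum.

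**Step 1: one complete block.** A 1:1 block of 4 has 4!/(2!·2!) = 6 equally likely sequences. Over these six:

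| Position in block | 1 | 2 | 3 | 4 | Sum | Mean |
|---|---|---|---|---|---|---|
| Chance that the assignment is certain from the history | 0 | 0 | 1/3 | 1 | 4/3 | 33.3% |
| Chance that the best guess is right | 1/2 | 2/3 | 2/3 | 1 | 17/6 | 70.8% |

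**Step 2: 30 participants in a single stratum (upper bound).** 30 = 7 × 4 + 2, that is, seven full blocks and two positions of an eighth.
- Certain: 7 × 4/3 + 0 = 9.3 of 30 (31.1%).
- Correct best guesses: 7 × 17/6 + (1/2 + 2/3) = 21.0 of 30 (70.0%).

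**Step 3: 30 participants in four strata.** Up to four last blocks stay incomplete, and the later, more predictable positions are the ones lost. As a worked case, take strata of 8, 8, 7 and 7.
- Certain: 2 × (2 × 4/3) + 2 × (4/3 + 1/3) = 5.33 + 3.33 = 8.7.
- Correct best guesses: 2 × (2 × 17/6) + 2 × (17/6 + 1/2 + 2/3 + 2/3) = 11.33 + 9.33 = 20.7.

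Averaged by simulation over random stratum sizes:

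| Assumed stratum shares | Certain, of 30 | Correct best guesses |
|---|---|---|
| Equal | 8.3 (27.7%) | 68.3% |
| 45/25/20/10% | 8.3 (27.7%) | 68.3% |
| Close to the Table 3 margins | 8.3 (27.8%) | 68.3% |

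The result hardly depends on the shares. Without blocking, the figures would be 0 and 50%.

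**Step 4: the two list holders.** They need no deduction, since every upcoming assignment is open to them.

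**Step 5: would varied block sizes help?** Each block returns to balance, so a guesser who always names the arm with fewer participants so far needs no knowledge of the block sizes. Simulated correct guesses under that rule:

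| Blocks | Four equal strata | Single stratum |
|---|---|---|
| Fixed 4 | 68.3% | 70.0% |
| Random 2 and 4 | 70.1% | 71.9% |
| Random 2, 4 and 6 | 67.8% | not run |
| Random 4 and 6 | 66.5% | not run |

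Blocks of 2 and 4 make guessing slightly easier, and the other mixtures change little. Custody of the list is what matters.

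**The case against.** **No one is shown to both know and decide.** Steering requires that the person who knows the next assignment also controls entry or its timing. The article gives the two list holders randomisation and allocation, and nothing says that they recruit, screen or judge eligibility. A reader might infer that the enrolling staff know the next assignment, but the text does not support that. An article may also leave such role details to the full protocol. This limits the point to what is stated: the three list functions are joined, and nothing in the text sets them apart from entry decisions.

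**Safeguards exist.** Access is limited to two people, the file is password protected, the code comes after baseline, and most exclusions are concrete conditions. All true, and these measures do protect against other staff reading the list. They do not bind the two who hold it.

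**Little of this pilot depends on the contrast.** This largely stands. The adherence, retention and SUS criteria are fixed thresholds, and the interviews come from app users. The 15 participants planned at the Tübingen clinic are not randomised. The article itself calls the effects preliminary.

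**AE monitoring is a separate matter.** In a waitlist design whoever monitors events will probably know the arm, however the list is kept. That stands, so the overlap aggravates the concentration of roles but is not itself a failure of concealment.

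**Printing the block size is weak evidence of harm.** The documents do not show that the article appeared before randomisation ended. The step 3 figures therefore rest on staff knowing the block size and keeping a tally by stratum.

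**Conclusion.** The point holds in a limited form. As described, upcoming assignments for the 30 GSU participants are not concealed from the two people who allocate, one of whom is the principal investigator. The plan names no step that keeps these two out of recruitment or eligibility decisions. For other staff, about 8 of 30 assignments are deducible with certainty, and best guesses are right about 68% of the time, given knowledge of the block size and a tally by stratum.

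Three stronger readings are tempting and should not be drawn:
- **Assignments were known to those enrolling.** The article does not say who enrols.
- **A third of assignments, or 10 of 30, are predictable.** That needs every block to fill. Since 30 is not a multiple of 4, the ceiling is 9.3 even in a single stratum.
- **The feasibility and usability conclusions are compromised.** They do not rest on the randomised comparison.

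Nor do the documents allow the size of any bias in the secondary outcomes or the AE comparison to be estimated. What can be shown is the opening for bias, not its effect. For a pilot this is worth correcting because it is cheap to do so; it does not invalidate the trial.

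**What to change.** **For participants not yet randomised.** Have an existing institute member with no role in recruitment, screening, testing or AE assessment generate and hold the list for the remaining places. That person releases one assignment at a time, once enrolment and baseline are complete. Sequentially numbered, sealed opaque envelopes prepared by the same person would serve equally well. State in the protocol who enrols, who holds the list and who releases assignments.

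**Block sizes.** Do not switch to random blocks of 2 and 4, for the reason shown in step 5.

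**If randomisation has closed.** Report who enrolled participants and who held the list, and name the lack of separation as a limitation of the between-group effects and of the AE comparison.

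**Cost.** A small administrative handover: a new list for the remaining places and a new holder of the password. No new staff, visits or measurements are needed. At submission 12 of the planned 45 had been enrolled across both sites, so most places were then still open.
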